**b. Aim and Objectives:**

This pilot study aims to explore the feasibility, acceptability and efficacy among dementia caregivers of the MBI delivered by VR technology (VR-based MBI) in the home environment. The specific research questions and hypotheses are as follows:

- **How do dementia caregivers perceive VR-based MBI?**

We will explore the feasibility, acceptability and understanding of using VR technology or audio to learn MBI among caregivers of people with dementia through a focus group qualitative study and a quantitative study using the Treatment Acceptability/adherence Scale. The readiness of caregivers to practice MBI at home after observing group sessions will also be explored.

- **Does the VR-based MBI offer additional benefits to psychological well-being compared with audio-based MBI and usual care?**

We will address this question through a 3-arm pilot randomized controlled trials (RCT). Using an 8-week audio-based MBI protocol and usual care as comparing conditions. We hypothesize that among caregivers of people with dementia:

**HP1:** The VR-based MBI group will show greater improvement in psychological well-being (**Primary Outcome**) than the audio-based MBI group, while the audio-based MBI group will show greater improvement than waitlist control group

Psychological well-being will be assessed through depression, anxiety and stress, as well as general wellbeing.

- **Does the VR-based MBI offer additional benefits to caregivers' mindfulness and quality of life, care recipients' quality of life and the relationship between caregiver and care recipient, compared with audio-based MBI and usual care?**

We will address this question through the RCT mentioned above. Compared with the audio-based MBI and usual care groups, we hypothesize that:

**HP2:** The VR-based MBI group will show greater improvements in caregiver burden, mindfulness level, and quality of life (**Secondary Outcomes**) than the audio-based MBI group, while the audio-based MBI group will show greater improvement than waitlist control group;

**HP3:** The relationship between VR-based MBI group caregivers and the care recipients (**Secondary Outcomes**) will show greater improvement than the audio-based MBI group, while the audio-based MBI group will show greater improvement than waitlist control group;

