### Procedures

The pilot RCT is a 3-arm, parallel, single-blinded trial to examine the feasibility, acceptability and potential effectiveness of the VR-based MBI, following the “Consolidated Standards of Reporting Trials” (CONSORT) guidelines(29). The intervention will last eight weeks with assessment periods at baseline, posttreatment, and 2-months follow-up. We will also conduct focus group for the intervention group after the intervention and at follow-up, using an interview guide. A consort diagram of procedures for our RCT pilot design and RE-AIM considerations is shown in Figure 1.

Figure 1. Consort diagram of procedures for randomised controlled trial design and RE-AIM considerations

[figure not shown]

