### Randomisation

Eligible participants will be randomly assigned into three groups: A) VR-based MBI (Intervention group) B) audio-based MBI group (control group) and C) Usual care group (Waitlist control group). Individual randomization using serially numbered opaque sealed envelopes (SNOSE) will be used to ensure that the allocation sequence is concealed from participants before the group allocation. The PA will prepare about 90 identical, opaque, sealed A5-sized envelopes, with a unique three-digit serial number on the cover of each envelope as an identifier. One-third of the envelopes will contain the action plan for the intervention group, another third the action plan for the audio-based MBI group, and the remaining envelopes the action plan for the waitlist control group. The intervention materials will be inserted into the envelopes, which will be sealed, shuffled, and numbered. Once a participant consents to participate in the study, the RA will open one envelope according to the sequence of the serial number and assign the participant to a treatment condition based on the action plan. No participants will be blinded to the given interventions.

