Participants will be invited to complete a face-to-face survey before and after the intervention to assess efficacy in terms of target outcomes. At 2-months follow-up, all three groups will be contacted for a telephone survey using the same assessment tools.

- **Adoption by target staff, settings, systems and communities**

We will track relevant participants information for calculating the indicators after recruitment. We will also collect caregivers' feedback on the adoption of the intervention through weekly phone calls and the focus group discussions after the intervention. During the recruitment and after the intervention period, we will also gather staff opinions on how this intervention can be integrated into their existing care practices and services and on the potential for wider adoption of the intervention within their organisation or across other institutions.

- **Implementation: consistency, costs and adaptations made during delivery**

We will track whether the intervention is being delivered as intended and any necessary adaptations made during the study. We will collect feedback from weekly call and focus group discussions after the intervention and exercise time records from the app.

- **Maintenance/sustainment of intervention effects in individuals and settings over time**

The long-term maintenance of the intervention's effects will be evaluated through follow-up assessments with participants and feedback from staff and settings that have adopted the VR-based MBI.

(vii) **Results analysis**

Quantitative data analysis plan

Quantitative data will be analysed using STATA 17.0. By intention-to-treat analysis, participants who are lost or refuse the follow-up will be treated as "no change in psychological well-being". Continuous variables will be checked for normal distribution. First, descriptive analyses will be conducted. Then, paired sample t-tests will be conducted to examine the level of outcome change between pre-test and post-test. Between-group t-tests will also be calculated to detect differences between the intervention and the control groups. A linear mixed-effects model (LMM) will be employed, accounting for both fixed effects (e.g., intervention group, time, and their interaction) and random effects (e.g., individual variability among participants). Confounding variables include demographic variables, self-reported physical health, health condition, social support, technology literacy, social service utilisation (38,39).

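### Paired and unadjusted t-tests stand unranked beside a mixed model that could test HP1 and that would gain precision at no cost by conditioning on the baseline score

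*Protocol*

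**What the plan says.** HP1, in section b (Aim and Objectives), has two parts. The first is "The VR-based MBI group will show greater improvement in psychological well-being" than audio; the second is "while the audio-based MBI group will show greater improvement than waitlist control group". Section c(ii), under Randomisation, labels the two comparators "B) audio-based MBI group (control group) and C) Usual care group (Waitlist control group". Under Procedures there are "assessment periods at baseline, posttreatment, and 2-months follow-up" (T0, T1, T2).

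Section c(vii), Results analysis, lists three inferential analyses in sequence:

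1. "paired sample t-tests will be conducted to examine the level of outcome change between pre-test and post-test".
2. "Between-group t-tests will also be calculated to detect differences between the intervention and the control groups". The text does not say whether these use post scores or changes, at which visit, or on which pairs of arms.
3. "A linear mixed-effects model (LMM) will be employed, accounting for both fixed effects (e.g., intervention group, time, and their interaction"), plus random effects for participants.

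The covariate sentence follows directly: "Confounding variables include demographic variables, self-reported physical health, health condition, social support, technology literacy, social service utilisation". None of the three analyses is named as the test of HP1, and no contrast is named.

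**The concern.** A paired test measures change within a set of people. Participants must report psychological distress to enter, so regression to the mean can produce improvement in every arm, waitlist included. A significant paired test in the VR arm therefore says nothing about VR against audio. Printed beside a non-significant one for audio, it invites exactly that reading.

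The between-group t-tests are described as intervention against controls. That can mean VR against audio, VR against each control, or VR against both pooled. None of these is audio against waitlist.

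The third issue is precision. With 30 per arm, every analysis of a pairwise contrast is imprecise, and the T0 score of each outcome is already collected. How T0 enters the analysis decides how much of that information is used.

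**Working it through.** **Inputs.** From the protocol: 30 per arm, and effect sizes of 0.4 to 0.54 (section c(i)), read here as standardised mean differences. Assumed because the protocol gives none: two-sided alpha 0.05, equal SD at T0 and T1 (set to 1), and pre-post correlation rho. The protocol has no power calculation to reproduce; it justifies 90 participants by feasibility and estimation.

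**1. Paired tests when the arms do not differ.** Let VR and audio both truly improve by 0.4 SD. The SD of change is sqrt(2(1 − rho)), so the standardised change is dz = 0.4 / sqrt(2(1 − rho)).

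- rho = 0.5: dz = 0.40, and the power p of one paired test with n = 30 is 56%.
- rho = 0.6: dz = 0.447, p = 66%.

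The arms are independent, so the chance that VR is significant and audio is not is p(1 − p): 0.56 × 0.44 = 25%, and 0.66 × 0.34 = 22%. A simulation with common improvements of 0.3 to 0.5 SD and rho of 0.5 to 0.7 gave 7 to 25%.

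**2. Coverage of HP1**

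| Analysis | VR v audio | Audio v waitlist |
|---|---|---|
| Paired t-tests | no | no |
| Between-group t-tests as worded | possible, not stated | not named |
| LMM, group × time | available, not named | available, not named |

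**3. Baseline and precision.** In the LMM as written, each arm has its own mean at T0. With complete data, the group-by-time term at T1 is then the difference between arms in mean change from T0 to T1. The variance per participant is:

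- post score: 1
- change score, or unconstrained interaction: 2(1 − rho)
- conditioned on T0 (ANCOVA, or T0 means constrained equal): 1 − rho²

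The saving against change is 1 − (1 − rho²) / [2(1 − rho)] = 1 − (1 + rho)/2 = (1 − rho)/2. The saving against the post score is 1 − (1 − rho²) = rho².

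| rho | Saving v change | Saving v post score |
|---|---|---|
| 0.3 | 35% | 9% |
| 0.5 | 25% | 25% |
| 0.6 | 20% | 36% |
| 0.7 | 15% | 49% |
| 0.8 | 10% | 64% |

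Power for one contrast, 30 v 30 (normal approximation):

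| Effect size, rho | Post score | Change | Conditioned on T0 |
|---|---|---|---|
| 0.4, 0.5 | 34% | 34% | 43% |
| 0.4, 0.7 | 34% | 52% | 58% |
| 0.54, 0.5 | 55% | 55% | 68% |
| 0.54, 0.7 | 55% | 77% | 83% |

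Conditioning on T0 gives the highest power in every row, and also at rho 0.3 and 0.8.

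**4. Covariate timing.** Figure 2 collects basic information at T0 only. No instrument listed for T1 or T2 measures social support, technology literacy or service use. EQ-5D-5L is repeated at T1 and T2, so only self-reported health has an evident post-baseline source.

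**The case against.** The strongest reply is that the valid analysis is already in the plan. The LMM covers all three arms, compares them, and uses T0 as a repeated outcome; both parts of HP1 can be read from its interaction terms. This stands. A reader might infer that HP1 has no valid test, and the protocol does not support that: what is missing is rank and named contrasts, which a separate analysis plan could supply.

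Other stronger readings also fail:

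- **That the t-tests throw the baseline away.** A paired test is built on the T0 score; its fault is the missing comparator. The between-group t-tests would use T0 if run on changes, and the protocol does not say which.
- **That omitting the T0 score from the covariate list is an error.** T0 is already an outcome in the LMM. The constraint is a gain in efficiency, not the repair of a bias.
- **That paired tests mislead in 45 to 49% of trials.** That is 2p(1 − p), which also counts audio significant and VR not. In the direction that favours VR it is half as much, and it does harm only if someone draws a between-arm conclusion, which the protocol does not announce.
- **That the model will adjust for variables altered by treatment.** Figure 2 gives little support beyond self-reported health.

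The trial is also a pilot meant to estimate effects and inform a larger trial. That lowers the weight. It does not make a comparator-free test suitable evidence for the directional hypotheses on designated primary outcomes, and it does not remove the precision gain.

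**Conclusion.** The point holds in a limited form. The protocol places paired pre-post t-tests and unadjusted between-group t-tests beside a suitable model as efficacy analyses without ranking them. The paired tests cannot address HP1, and the between-group t-tests as worded leave out half of it.

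The LMM can address HP1 but is less precise than the data allow. The variance of the T1 contrast can fall by (1 − rho)/2, that is 10 to 35% for rho from 0.8 to 0.3. Against a t-test on post scores it can fall by rho², that is 9 to 64% over the same span. These figures assume equal SDs at T0 and T1, complete data, and a correlation that the protocol does not state. The 22 to 25% in the paired-test illustration further assumes a common improvement of 0.4 SD and rho of 0.5 to 0.6.

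This is a free improvement of moderate severity, not a defect that must be cured before a pilot can start. Covariate timing is a minor part of it.

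**What to change.** In section c(vii):

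- Name one analysis for HP1 to HP3: an LMM on T0, T1 and T2 with time and arm-by-time terms and arm means constrained equal at T0, or ANCOVA on the T0 score.
- State two contrasts at T1, VR minus audio and audio minus waitlist, each with a 95% confidence interval.
- Keep the paired and between-group t-tests as description only.
- Use only T0 values of any further covariates, and call them prognostic covariates; confounders is the wrong term in a randomised comparison.

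The cost is a change of wording. Data, visits, sample size and software stay the same, and the only thing given up is the t-tests as evidence of efficacy.

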## **Ethics consideration**

### Major ethical issues

The study follows the Declaration of Helsinki on medical protocol and ethics. Ethics approval will be obtained from the HKU/HA HKW Institutional Review Board (HKU/HA HKW IRB). Participants are voluntary to join the study. A written informed consent, which will include the research title, purpose, explanation of the research, and the procedures of the study, will be obtained from each eligible participant. Risks and benefits are also explained clearly to the participants. Participants have the right to withdraw from the study at any time. They will be protected from discomfort and harm during the study. Further, anonymity and confidentiality of the participants will be strictly protected.

## **Data Protection**

Strict confidentiality will be kept and that the information obtained in the study will be used for research purposes only. The data collected in this study will be kept for 5 years after the study, and personal identifiers will be removed for long term retention of the research data. Participant will not be identified by name in any report of the completed study.

## **Funding Source**

This study will be funded by the Health and Medical Research Fund (HMRF).

